### Participant Involvement by Group

Participant recruitment began in October 2023 and is expected to continue until July 2024. Participants will complete the screening and informed consent process with research staff and will be randomized upon completion of their baseline surveys. Participants that have been randomized to the intervention group will be matched with a facilitator in their region. The facilitators will follow up after randomization and schedule the 1-hour-long information-sharing session (ie, empowerment component) and then continue to follow up with the weekly calls for 12 weeks (ie, social support component). Quantitative survey data will be collected from all the participants at 3- and 9-month follow-ups. Follow-ups with participants in the AIM intervention group will take place 3 and 9 months after their final social support session. For participants randomized to the comparison group, follow-ups will take place 3 and 9 months after they have completed the baseline surveys. We estimate the total time commitment for participants to be 11 hours for those randomized to the AIM intervention group and 4 hours for those in the comparison group. Table 2 breaks down the estimated time commitment for each study activity.

**Table 2 table2:** Participant involvement by group.

Study activity	Time commitment for participants in the AIM^a^ intervention group (hours)	Time commitment for participants in the comparison group (hours)
Informed consent process	0.5	0.5
Baseline data collection	1.5	1.5
Empowerment component	1	—^b^
Social support component	6	—
3-month follow-up	1	1
9-month follow-up	1	1
Total time commitment	11	4

^a^AIM: advocacy intervention for midlife and older women.

^b^Did not participate.

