**Methods:**

This trial is a 2-arm, unblinded, parallel, pragmatic randomized controlled trial with a qualitative component. Eligible participants will be women who live in the Maritime provinces of Canada (New Brunswick, Nova Scotia, and Prince Edward Island), who are in midlife and older (aged approximately ≥50 years), and who are currently in a relationship with an abusive partner or have recently left an abusive partner. Facilitators will be trained to deliver the intervention. The intervention will be entirely virtual and will consist of 2 components: (1) an empowerment component, which will involve sharing resources and information with the women; and (2) a social support component, which will include providing support and encouragement to women for 12 weeks. Quantitative effectiveness data will be collected from all trial participants at baseline, 3 months after the intervention, and 9 months after the intervention about the incidence and severity of IPV, physical and mental health, and safety behaviors and strategies. Qualitative interviews will be conducted with the facilitators and intervention group participants. Control group participants will receive a static, nontailored version of the advocacy intervention for midlife and older women (AIM) intervention materials after baseline data collection.

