#### Components of AIM

The empowerment component is derived from the empowerment model by Dutton [37] to increase women’s safety. This component will involve the facilitator providing a 1-hour-long individual one-on-one information-sharing session with the participants that will be delivered virtually by telephone or video call. These sessions will include providing information on recognizing increased danger and how to use an individualized safety plan adapted for older women, providing information about cycles of violence, providing community and legal resources, and developing goals and strategies for the future. In addition to discussing this information, print materials will be provided electronically (via email) or in hard copy (via postal mail). Thus, this component clearly contributes to awareness raising and also empowers the women to develop changes in the future.

The social support component is based on the social support theory by Cohen [38] that involves tangible and perceived social support to contribute to health and well-being. This component will involve the facilitator scheduling weekly telephone or video calls over a course of 12 weeks at a time that is convenient to the participant. The duration of calls is variable and would average approximately 20 minutes per call. The calls are intended to provide encouragement and support and to answer questions the participant may have about using or applying the resources provided in the empowerment component. There are no specific or scheduled topics that are planned for each session. These are very individualized and based on the women’s needs and questions that each woman may wish to discuss. For example, facilitators will be prepared to help women with recognizing their past abuse and processing the abuse as well as providing support to women who are undergoing court proceedings and legal issues. The social support provided through the weekly contact is a key component of the intervention in addition to the topics discussed.

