#### Potential Harms to Participants

For participants living at home with the perpetrator, the participant may be at risk if the perpetrator finds out they are participating in the study. We will ensure personal safety of the participants in various ways at each stage of the research, including participant recruitment. The participants are welcome to participate virtually at a time and location that is chosen by them. If they need to end participation at any time, they are welcome to do so, and the facilitator will follow up at a time that is suitable and safe for them. As both the empowerment and social support components are delivered individually to participants, we can be very flexible about when the intervention is delivered.

The facilitators will teach the participants about ensuring digital security (eg, clearing browser history) during the empowerment component of the intervention. The participants will also be provided with information about local resources and services that are available. If the participant is in immediate danger during the time the facilitator is talking with them, they will instruct the participant to call 911, and if that is not possible, they will call 911 on the participant’s behalf.

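### The nominal 3- and 9-month visits are timed from the last support call in the AIM arm but from baseline in the comparison arm, so arm is confounded with about 11 to 12 or more weeks of elapsed time

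*Protocol article*

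**What the plan says.** Two consecutive sentences under Participant Involvement by Group set the follow-up clock by arm. For AIM: "Follow-ups with participants in the AIM intervention group will take place 3 and 9 months after their final social support session". For the other arm: "For participants randomized to the comparison group, follow-ups will take place 3 and 9 months after they have completed the baseline surveys".

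The same section says that participants "will be randomized upon completion of their baseline surveys", so completion of baseline is effectively the date of randomisation in both arms. After randomisation an AIM woman is matched with a facilitator, who will "schedule the 1-hour-long information-sharing session (ie, empowerment component) and then continue to follow up with the weekly calls for 12 weeks". Components of AIM likewise describes "scheduling weekly telephone or video calls over a course of 12 weeks". The comparison group receives its printed or emailed package after baseline and no further contact about it (Comparison Group).

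Table 1 in Outcomes Measured gives both arms the same column labels, 3 months and 9 months. Statistical Analysis compares the groups at 3 and 9 months, by repeated measures analysis of variance for continuous variables and a chi-square or Fisher exact test for categorical ones. The abstract says: "Quantitative effectiveness data will be collected from all trial participants at baseline, 3 months after the intervention, and 9 months after the intervention". The Limitations section does not mention the difference in timing.

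**The concern.** Randomisation makes the two groups comparable at equal time since randomisation. Here the visits that share a label are not at equal time, and the gap runs the same way at every follow-up: AIM women are always assessed later. The planned contrast therefore estimates the effect of AIM plus whatever would have changed anyway over the extra weeks.

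That change could matter in this population. Women enter while in an abusive relationship or within a year of leaving one, and Eligibility Criteria describes leaving as a process that often involves leaving and returning several times. Fear of the partner, decisional conflict, depressive symptoms, social support and safety strategies could all plausibly shift over about three months without any intervention. Natural improvement would be credited to AIM, and natural deterioration would be counted against it. All the listed scales are collected at these visits, so all are affected.

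**Working it through.** **Inputs from the protocol article.** Comparison visits: 3 and 9 months from baseline completion. AIM visits: 3 and 9 months from the final social support session. Social support: 12 weekly calls over 12 weeks. Target analysed size: 30 per arm (Sample Size).

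**Not given, so assumed.** The time needed for matching and the 1-hour session; the rate of natural change; the significance level.

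**Step 1: gap between the clocks.** One month = 365.25/12 = 30.44 days.

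- Shortest case for a full course: the first call comes at once after randomisation. Twelve weekly calls span 11 intervals, so the gap is 11 × 7 = 77 days, or 77/30.44 = 2.53 months.
- Nominal case: 12 weeks = 84 days, or 84/30.44 = 2.76 months.
- Slower start: if matching and the first session add 4 weeks (assumed), 16 weeks = 112 days, or 3.68 months.

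**Step 2: time since randomisation at each visit.** AIM time = gap + nominal months.

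| Gap | AIM, 3-month visit | Comparison | Ratio | AIM, 9-month visit | Comparison | Ratio |
|---|---|---|---|---|---|---|
| 77 days | 5.5 months | 3.0 | 1.84 | 11.5 months | 9.0 | 1.28 |
| 84 days | 5.8 months | 3.0 | 1.92 | 11.8 months | 9.0 | 1.31 |
| 112 days | 6.7 months | 3.0 | 2.23 | 12.7 months | 9.0 | 1.41 |

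At the first follow-up AIM women are nearly twice as far from randomisation as comparison women.

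**Step 3: illustration of the bias.** Spurious difference = gap in months × assumed linear drift in SD per month. For a two-sided two-sample t-test at an assumed 5% level with 30 per arm, the noncentrality is the difference × √(30/2) on 58 degrees of freedom (critical value 2.002).

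| Assumed drift (SD/month) | 77 days: difference, type I error | 84 days: difference, type I error |
|---|---|---|
| 0.02 | 0.05 SD, 5.4% | 0.06 SD, 5.5% |
| 0.05 | 0.13 SD, 7.7% | 0.14 SD, 8.2% |
| 0.10 | 0.25 SD, 16.1% | 0.28 SD, 18.3% |

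The plan states no effect size, SD, significance level or power, so it has no figure of its own to reproduce here.

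**Step 4: calendar.** Recruitment is expected to continue until July 2024 (Participant Involvement by Group), and data collection ends in January 2025 (Results). Counting back 9 months (274 days) from 31 January 2025, a comparison woman must be enrolled by about the start of May 2024 to reach her last visit. An AIM woman, with 84 more days, must be enrolled by about 9 February 2024. An AIM woman enrolled at the end of July 2024 would have her last visit around 23 July 2025. If the January 2025 date were enforced, final-visit missingness would also differ by arm.

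**The case against.** The strongest defence is that the design looks deliberate. Each arm is timed from the end of what it received: comparison women get their package just after baseline, AIM women finish with the last call, and the abstract speaks of time after the intervention. On that reading the abstract is not plainly wrong, and durability after the end of treatment is a reasonable question. This stands as an account of intent. It does not remove the confounding, because comparability rests on time since randomisation.

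A reader might infer several stronger points that the document does not support:

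- **That 84 days is the minimum gap.** It is not: twelve weekly calls span 11 intervals, so a full course can end after 77 days. A woman who completes only 10 or 11 calls remains in the analysis and could have an earlier anchor if her last attended call counts as the final session.
- **That early stoppers distort the planned analysis through their own anchor.** Statistical Analysis excludes AIM women with fewer than 10 of 12 calls, so most contribute no data. That exclusion is a separate matter.
- **That no analysis could separate treatment from time.** Comparison data at 0, 3 and 9 months bracket the AIM visit at about 5.8 months, so interpolation is possible under an assumed trajectory. The visit at about 11.8 months needs extrapolation. The accurate statement is that separation needs assumptions the data cannot test.
- **That the calls will overrun.** The remark in Potential Harms to Participants that "we can be very flexible about when the intervention is delivered" concerns safe timing for women living with a perpetrator. It allows for slippage but does not predict it.
- **That the error rates are estimates.** They rest on assumed linear drift and a single-visit t-test, whereas the plan has repeated measures analysis over several scales. At the low end the inflation is trivial.

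**Conclusion.** The point holds. The two clocks differ in plain words, the analysis treats the visits as common occasions, and nothing in the document aligns, adjusts for or acknowledges the gap. For a full course of calls the offset is about 11 to 12 weeks, and longer if matching or calls are delayed: about 5.5 to 5.8 against 3.0 months, and about 11.5 to 11.8 against 9.0 months. This depends only on the stated schedule.

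The resulting bias cannot be signed or sized from the document. The range of 0.05 to 0.28 SD, with type I error of about 5.4% to 18%, is conditional on the assumed drift and the simplified test. The flaw lies in when data are collected and touches every between-arm follow-up comparison, so it should be corrected in the schedule and not left to the analysis.

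**What to change.** Schedule both arms from the date of randomisation with identical visit windows, whether or not the calls are finished. One option keeps the AIM timing nearly as it is: 12 weeks plus 3 months and 12 weeks plus 9 months, that is about 6 and 12 months for everyone. Record the actual date of every assessment. Align the abstract, Table 1 with its surrounding text, and Participant Involvement by Group so that all define the visits in the same way.

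For women already assessed on the present clock, record actual days since randomisation and model outcome on time since randomisation. This is a partial salvage that depends on the assumed trajectory, so the offset should also be reported as a limitation.

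Costs: no visits are added, but comparison visits move about 12 weeks later. Recruitment began in October 2023, so some comparison women may already have had their 3-month visit and would be on a mixed clock. AIM women whose calls run late would be seen less than 3 months after their last call. The January 2025 end of data collection needs restating, but the present AIM schedule already exceeds it for women enrolled after about early February 2024, and the common clock does not push the last visit materially beyond what AIM already requires.

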### Data Management

REDCap software will be used to store and manage the study data [42]. The only individuals with access to the REDCap data will be the research coordinator and the research assistants. The research coordinator and the research assistants will enter the participants survey responses directly into the REDCap forms at baseline and 3- and 9-month follow-ups.

### Statistical Analysis

Quantitative data will be exported from REDCap as a spreadsheet and then uploaded into SPSS (IBM Corp) for quantitative analysis. Participants in the AIM intervention group need to complete the empowerment component and attend at least 10 out of 12 weekly calls of the social support component for their quantitative data to be included in the analysis.

Descriptive statistics will provide a profile of study participants, including demographics for the whole sample and for those in each of the 2 groups. The provisional effect of the intervention will be tested using a prospective chi-square test of independence between the 2 groups for categorical data (Fisher exact test) at 3 and 9 months. Repeated measures analysis of variance will measure mean differences between the groups on continuous variables at 3 and 9 months.

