## Methods

### Trial Design

This trial is a 2-arm, unblinded, parallel, pragmatic RCT [21] registered in the International Standard Randomized Controlled Trial Registry (ISRCTN30646991). This protocol is reported according to the SPIRIT (Standard Protocol Items: Recommendations for Interventional Trials) guidelines [22]. The intervention has been modeled using the Template for Intervention Description and Replication checklist [23], and the results will be reported according to the CONSORT (Consolidated Standards of Reporting Trials) statement for RCTs [24]. Figure 1 displays the CONSORT flow diagram for this RCT.

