#### Comparison Group

The comparison group will receive a static, nontailored version of the AIM intervention materials after baseline data collection. They will be asked if they prefer to receive these materials via email or postal mail. The document will include a condensed version of the empowerment component and information about the dynamics of abusive relationship, warning signs of abuse for older adults, materials on safety planning and digital safety, local and national IPV resources, and guidance for setting goals for the future. The participants in the comparison group will not receive any further contact from the research team or facilitators to discuss these materials. Textbox 1 outlines the features (ie, information and support) that participants will receive depending on what group they are randomly assigned to.

Features of the advocacy intervention for midlife and older women (AIM) intervention group and comparison group.

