### Sample Size

For the quantitative portion of the study (ie, the RCT), we determined an appropriate sample size that would be sufficient to contribute to the evidence base. We reviewed the sample sizes analyzed in the systematic review we conducted, the sample sizes of the studies focused on women experiencing IPV in midlife and older, and the sample size calculations in the study from which we have adapted the program [34]. We used our prior experience in recruiting midlife and older women as well as the resources available to conduct this research. We then concluded that recruiting 30 participants per arm is sufficient, that is, 30 women randomized into the intervention arm and 30 women randomized into the control arm. To account for a 15% attrition rate identified in a similar study [39], we will recruit 70 women, with 35 randomized to each group.

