### Random Assignment of Interventions

REDCap (Research Electronic Data Capture; Vanderbilt University) software will be used to store and manage the data collected from participants. REDCap is a web-based software application that securely stores research data [42]. The random allocation sequence was generated using REDCap [42]. The research coordinator developed an allocation table that included each option for random assignment that was stratified by the province of residence. This involved creating an Excel (Microsoft Corp) table with each intervention option (ie, intervention and control) in one column and province of residence (ie, New Brunswick, Nova Scotia, and Prince Edward Island) in another column. We wanted to ensure that an equal number of participants were randomized to the intervention and control group within each province in a balanced manner. Therefore, there were 6 study options uploaded to the software. Once the allocation table was uploaded to REDCap, it was locked and could not be modified.

REDCap will be used to randomize the participants. After a participant has completed the baseline surveys, the researcher will press the “randomize” button to determine the participant’s group allocation. While assignment to the groups is random, once assigned, participants are not blinded to their group. The researcher will inform each participant of the group they are allocated to at the end of the baseline interview. The research staff (research coordinator and research assistant) will be responsible for screening, consenting, enrolling, and using Recap’s randomization module to allocate participants to their study group.

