### Qualitative Component

We will conduct interviews with approximately 12 participants of the AIM intervention group. This sample size is sufficient when using a qualitative descriptive approach to generate rich, detailed descriptions and meaningful data [49,50]. In these interviews, we will use maximum variation sampling to include women who have specific characteristics (eg, francophone, new immigrant, and rural) and ask them about their perceptions of the program and their recommendations for further program development. We will also invite any intervention group participants who did not complete the AIM program to participate in an interview to learn about their experiences in the program and ask for any recommendations they may have to help improve the program. All facilitators who deliver the AIM intervention to trial participants will be invited by telephone or email by the research coordinator to complete a qualitative interview. While all will be invited, we hope that at least 4 to 5 will volunteer to participate in the interview.

At the 9-month follow-up data collection point, the research coordinator will invite women from the AIM intervention group to take part in a virtual interview. To be eligible to be invited for the interview, participants must have completed the empowerment component and at least 10 out of 12 social support sessions. In these interviews, the research coordinator will try to recruit a diverse sample of women who represent the characteristics of the participants and ask them about their perceptions of the program and their recommendations for further refinement of the program to meet the needs of diverse midlife and older women. The informed consent form will be shared by email or by postal mail.

The research team will also conduct an exploratory qualitative analysis on the data recorded by the program facilitators. Facilitators will be instructed to record the date and length of each session and take notes. The notes will detail the topics discussed with participants, the support and resources offered to participants, and any questions or concerns raised by the participants. The analysis of this exploratory data will summarize what topics are discussed and what supports are provided to participants.

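### AIM women's data are analysed only if they complete the empowerment session and at least 10 of 12 calls; the comparison group faces no such condition, so the analysed groups are no longer those formed by randomisation

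*Protocol article*

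**What the plan says.** The Statistical Analysis section states: "Participants in the AIM intervention group need to complete the empowerment component and attend at least 10 out of 12 weekly calls". Meeting this threshold decides whether a woman's survey results are used at all; it is not merely a definition of adherence. The section then names the tests (chi-square or Fisher for categorical data, repeated measures analysis of variance for continuous data) and gives no other analysis population.

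The other relevant statements are:

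- Comparison Group: these women are sent written materials, and "The participants in the comparison group will not receive any further contact from the research team or facilitators to discuss these materials". They have no attendance requirement to meet or fail.
- Random Assignment of Interventions: "After a participant has completed the baseline surveys, the researcher will press the “randomize” button to determine the participant’s group allocation". All call attendance therefore comes after allocation.
- Participant Involvement by Group: "Quantitative survey data will be collected from all the participants at 3- and 9-month follow-ups". For AIM women, both surveys are timed from their last social support session; for the comparison group, from baseline.
- Qualitative Component: "We will also invite any intervention group participants who did not complete the AIM program to participate in an interview". Non-completion is expected.
- Trial Design: "This trial is a 2-arm, unblinded, parallel, pragmatic RCT". The Objectives section says the goal is to test effectiveness.
- Sample Size: 30 per arm is judged sufficient, and "To account for a 15% attrition rate identified in a similar study [39], we will recruit 70 women, with 35 randomized to each group".

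**The concern.** Randomisation makes the two groups comparable at allocation. Keeping AIM women according to something they do afterwards, with no counterpart in the other arm, gives up that comparability. The analysis would compare women who kept up at least 10 of 12 calls (83%) with comparison women of every kind, including those who would not have kept up such calls had they been offered.

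It also changes the question. A pragmatic effectiveness trial asks whether offering AIM helps the women to whom it is offered. The Eligibility Criteria section describes women leaving and returning to partners repeatedly, and the Potential Harms section allows for sessions being ended when necessary. Women whose circumstances interrupt the calls belong to the population of interest, and the rule removes them. According to the Dissemination section, a finding of effectiveness leads to public release of the programme, so the analysis set matters beyond this trial.

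This is not a detail that can be left to a separate analysis plan. The article fixes the rule, and it is the only analysis set given.

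**Working it through.** **1. The plan's own figure.** Inflating 30 per arm for 15% attrition gives 30 / 0.85 = 35.3 per arm and 60 / 0.85 = 70.6 in total. The stated 35 and 70 agree within rounding. Going back, 35 × 0.85 = 29.75, so the allowance is used up by 15% loss, and no separate allowance for the attendance rule is stated. The 30 itself is not tied to a stated effect size, power or alpha, so it cannot be recalculated.

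**2. Size of the selection bias.** The documents give neither the share of AIM women who will meet the rule nor how attendance relates to outcome. Both are assumed here. Let *a* be the share meeting the rule and *r* the correlation between attendance propensity and a better outcome, with no true effect. Selecting the top *a* of a normal propensity shifts the AIM mean by

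bias = r × φ(c) / a, with c = Φ⁻¹(1 − a), in SD units.

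At a = 0.7, φ(c)/a = 0.497, so r = 0.3 gives 0.15 SD and r = 0.5 gives 0.25 SD. Two-sided type I error comes from the noncentral t distribution at a nominal 5%, with 30 comparison women and 35 × 0.85 × a AIM women (27, 24, 21 and 15).

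| Share meeting the rule | Bias, r = 0.3 to 0.5 (SD) | Two-sided type I error |
|---|---|---|
| 90% | 0.06 to 0.10 | 5.5 to 6.5% |
| 80% | 0.11 to 0.18 | 6.6 to 9.6% |
| 70% | 0.15 to 0.25 | 8.1 to 13.7% |
| 50% | 0.24 to 0.40 | 11.5 to 23.4% |

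With r = 0 there is no bias. With r = −0.3 the bias has the same size as for r = 0.3 but favours control.

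A simulation (40,000 runs per setting, 30 per arm before exclusion, shares of 60 to 90%) agrees. At 70% and r = 0.3 the bias is 0.15 SD, and false wins for AIM are 7.5% against a nominal 2.5%. Analysing all women as allocated in the same runs gives no bias and a two-sided error of 4.8 to 5.2%.

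**3. What the planned test could change.** Step 2 uses a single follow-up score. The plan is repeated measures analysis of variance, and every scale is also measured at baseline. Suppose that baseline enters as a time level, that attendance is related to outcome only through baseline, and that baseline and follow-up correlate 0.7 (assumed). At a = 0.7 and r = 0.3:

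- attendance-baseline correlation = 0.3 / 0.7 = 0.429
- baseline difference = 0.429 × 0.497 = 0.213 SD
- follow-up difference = 0.3 × 0.497 = 0.149 SD
- difference in change = 0.149 − 0.213 = −0.06 SD, against AIM

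A baseline-adjusted contrast would be about 0 in that case. Selection related to later change, such as stopping the calls because things got worse or better, is not removed.

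**4. Numbers analysed.** If calls were attended independently (assumed), per-call attendance of 95%, 90%, 85% and 80% would give 98%, 89%, 74% and 56% of AIM women meeting the rule. That is about 34, 31, 26 and 20 of 35, before any loss to follow-up. At 70% meeting the rule, the analysed arm is 35 × 0.7 = 24.5 if everyone lost to follow-up is also a non-attender, and 35 × 0.85 × 0.7 = 20.8 if the two losses are independent: about 21 to 25. With 30 comparison women, the effect detectable with 80% power (two-sided 5%, noncentral t) rises from 0.74 SD at 30 to 0.81 SD at 21.

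**The case against.** The strongest reply is that direction and size are unknown. A reader might infer that the plan is shown to favour AIM. The documents do not support that, because nothing in them reports how attendance relates to outcome. Women in crisis may miss calls, but women who improve or leave the partner may also stop calling. Nor do the documents suggest low adherence: calls are booked at the participant's convenience and delivery is described as flexible. At 80 to 90% adherence the illustrated error is 5.5 to 9.6%. The planned repeated measures analysis could also cancel or reverse selection that works through baseline. All of this stands, and it limits the figures to illustrations. It does not rescue the rule, since the comparison is unbiased only if attendance is unrelated to outcome or the analysis happens to remove the relation. Neither can be assumed.

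A reader might also infer that all comparison women are kept. The article only places no condition on them; those lost to follow-up will be missing there too.

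Nor is it established that the AIM arm must fall to 21. Attrition is not defined in the Sample Size section. If it already covers programme non-completion, about 30 is what was planned. If not, loss to follow-up and non-attendance probably overlap, which makes the shortfall smaller. The power loss is modest and secondary to the bias.

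**Conclusion.** The point holds and should be corrected before analysis. The only analysis set in the article selects on post-randomisation attendance in one arm, so the analysed groups are not the randomised ones. This conflicts with the pragmatic effectiveness aim. It follows from the text and needs no assumption.

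The size does need assumptions. With an attendance-outcome correlation of 0.3 to 0.5 and a simple test on one follow-up score, the spurious benefit runs from 0.06 SD (90% adherent, correlation 0.3) to 0.40 SD (50% adherent, correlation 0.5). Type I error runs from about 5.5% to 23%. Bias towards AIM is the likelier direction but is not demonstrated. That a significant result would be nothing but selection is also more than the documents support. An analysed AIM arm below 30 is conditional on the 15% allowance not already covering programme non-completion.

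**What to change.** 1. Delete the attendance condition from the Statistical Analysis section. Define the primary analysis as all randomised women in their allocated arm, using all baseline, 3-month and 9-month data collected.
2. State that AIM women are surveyed whatever number of calls they attended. Time the surveys from a point that exists for every woman, such as randomisation or baseline. The present anchor, the final social support session, is undefined for a woman who never starts and ambiguous for one who stops early.
3. Keep the at-least-10-of-12 set only as a labelled supportive analysis. A complier-average analysis is optional. If one is done, state its assumption that attending 1 to 9 calls brings no benefit, which is hard to defend for a support programme delivered call by call.
4. Say in the Sample Size section whether the 15% covers loss of survey data, programme non-completion or both.

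Cost: no new data collection, because surveys are already planned for all participants. The analysis rule and the follow-up timing need small wording changes. The estimate may be less favourable to AIM once women who did not complete the programme are included.
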